#### 9.4.2 Data Acquisition

Cost and feasibility data will be obtained using hospital cost data (antibiotics and pharmacy FTE), questionnaires, and notes/observations created during interactions with hospital personnel. Patient endpoint data will be obtained from electronic pharmacy antibiotic prescribing data (start and stop dates for all antibiotics) and hospital databases (e.g., ADT data for admit/discharge dates for all patients; patient status database (mortality); and diagnosis code databases).

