#### Secondary Stewardship Hypotheses

1. Antimicrobial restriction and preauthorization will be less resource-intensive for hospitals (e.g., set-up time, approval time, personnel resources) than post-antibiotic prescription review (PAR) and feedback.
2. Prescribers will consider preauthorization to be intrusive to clinician autonomy and patient care.
3. The cost of performing PAR by a trained pharmacist will be offset by the cost savings achieved by decreasing antimicrobial cost.
4. Both strategies will lead to a decrease in utilization for targeted antimicrobials relative to utilization in the period prior to implementation of the stewardship strategies.
5. Decreases in targeted antimicrobial utilization from antimicrobial restriction will be offset by increases in use of alternative antibiotics.
6. The strategy of antimicrobial restriction and preauthorization will be less effective at reducing overall antimicrobial use than the strategy of prospective audit and feedback, as it will not shorten duration of antimicrobial therapy.

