#### 3.3.2 Secondary Objectives and Outcomes

To estimate and compare the time required of the pharmacist to administer each strategy

1. To estimate and compare the resource utilization of each strategy, where resource utilization includes pharmacist time and cost of antibiotics.
2. To compare the days of therapy (DOT) for antibiotics of interest between each strategy

DOT will be measured as the number of days a patient receives each targeted and alternative antibiotic during the hospital admission.

3. To compare patient-specific outcomes between each strategy, including but not limited to the following:

a. Total hospital days

b. Intensive care unit admission

4. To compare the prescriber and pharmacist perceptions of the two stewardship strategies

5. To develop integrated measures of benefit: risk for AS (based on days of therapy, hospital days, and patient outcomes such as ICU admission and survival) and compare strategy effects with respect to these measures

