### 3.5.2 Study Limitations

#### Drug Shortages

A known limitation of this study is that there were drug shortages among the antibiotics of interest while the study was ongoing. This means that differences observed between the two interventions, or the lack of differences observed may be related to drug availability and not the intervention.

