408         than one intervention over the course of a year)

409 Signs and symptoms

410     • Fever

411     • Leukocytosis

412     • Hypotension

413     • Cough or Sputum production

414     • Other signs or symptoms

- 415 • List of other/specifies
- 416 • Number of signs and symptoms per intervention

417 Culture data

- 418 • Culture data available for review (yes/no)
- 419 • If yes, was the culture data reviewed
- 420 • If yes, did it help inform the recommendation?

421 Intervention outcome

- 422 • Was the recommendation followed?
- 423 • Was there an ID consult after the intervention?
- 424 • ICU admission

425 Ultimate Infection diagnosis related to recommendation

- 426 • Pneumonia
- 427 • UTI
- 428 • Meningitis
- 429 • Surgical site infection
- 430 • SSTI
- 431 • Colitis
- 432 • Bacteremia
- 433 • Sepsis with unknown source
- 434 • No infection
- 435 • Other
- 436 • List of other, specify

437 **10. Days Of Therapy**

438 **Purpose:** To address Secondary objective 2, to compare DOT for antibiotics of interest between each  
439 strategy.

440

- 441 • Days of therapy (DOT) for targeted and alternative antibiotics
  - 442 ○ Per the protocol, DOT will be measured as the number of days a patient receives
  - 443 each targeted and alternative antibiotic during the hospital admission

444 The three targeted antibiotics are:

- 445 • Anti-pseudomonal carbapenem of choice at the study hospital
- 446 • Vancomycin
- 447 • Piperacillin-tazobactam.

448 The alternative antimicrobials of interest are:

- 449 • Fluoroquinolones
- 450 • Cephalosporins
- 451 • anti-MRSA systemic antimicrobials (e.g., nafcillin, daptomycin, linezolid, ceftaroline,
- 452 clindamycin, and TMP-SMX).

Among admissions with an included antibiotic, by hospital

- Table 1
  - Year prior to study
  - Period 1 Admission with Included antibiotic, no intervention
  - Period 1 Admission with stewardship intervention
  - Period 2 admission with Included antibiotic, no intervention
  - Period 2 admission with stewardship intervention
- Table 2
  - Period 1 (all admissions with an antibiotic of interest)
  - Period 2 (all admissions with an antibiotic of interest)
- Table 3
  - For 3 contrasts (PAR vs Historical year; Res/PreA vs historical Year; PAR vs Res/PreA)
  - Difference in proportion used drug with 95%CI
  - Difference in Mean DOT with 95% CI

For each antibiotic,

- proportion of admissions where the antibiotic was received
- DOT for the antibiotic

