  - Admissions where the antibiotic was not received will have a DOT of 0.
- Modeling (1 model for each of the antibiotics of interest)
  - The purpose of the model is to look at the effect of the intervention on DOT for each antibiotic of interest
  - Dependent variable = DOT for each antibiotic
  - Adjusting for hospital, study period, AS strategy, calendar time, demographic variables
  - The interactions of study period \* strategy, hospital \* study period, hospital \* strategy, will be explored.

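### SAP section 10 analyses days of therapy only drug by drug, so hypotheses 5 (offset by alternatives) and 6 (overall use) have no planned contrast or confidence interval

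*Combined protocol and SAP*

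**What the plan says.** The protocol (3.1.3) and SAP (3.3.2, objective 2) define the outcome agent by agent: "DOT will be measured as the number of days a patient receives each targeted and alternative antibiotic during the hospital admission". SAP section 10 follows that definition throughout. For each antibiotic it reports the proportion of admissions that received it and the DOT, with zero for admissions that did not. Table 3 then gives, for three contrasts (PAR vs historical year, restriction/preauthorization vs historical year, PAR vs restriction/preauthorization), the difference in proportion and "Difference in Mean DOT with 95% CI". The modelling step is "Modeling (1 model for each of the antibiotics of interest", with "Dependent variable = DOT for each antibiotic". No total is defined for the three targeted drugs, for the alternatives, or for both.

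Two hypotheses in SAP 3.3 (also Protocol 3.1.1) concern quantities across drugs. Hypothesis 5: "Decreases in targeted antimicrobial utilization from antimicrobial restriction will be offset by increases in use of alternative antibiotics". Hypothesis 6 states that restriction and preauthorization "will be less effective at reducing overall antimicrobial use than the strategy of prospective audit and feedback".

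The section 10 tables are headed as covering admissions with an included antibiotic, although Table 2 refers to all admissions with an antibiotic of interest. SAP section 6 counts included and other antibiotics separately, and the SAP defines neither label.

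**The concern.** Stewardship can lower use of a restricted drug simply by moving patients to another one. Hypotheses 5 and 6 exist to tell a net reduction from a move. A set of separate per-drug differences, each with its own interval, shows the pieces but gives no uncertainty for the net change. A report that follows section 10 could describe targeted drugs falling and alternatives rising. It could not say, with an interval, how much of the fall remained, or which strategy left total use lower.

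The analysis population adds to this. If included means targeted, a patient who is denied a targeted drug and receives only an alternative leaves the DOT tables. That is the patient in whom an offset would appear.

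**Working it through.** **1. The plan's own figure.** Protocol 9.1 states 97% power within a hospital for a difference of 0.05 from 0.50, with n = 3000 per period and alpha 0.05.
- Pooled SE = √(2 × 0.525 × 0.475 / 3000) = 0.01289.
- Unpooled SE = √((0.25 + 0.2475) / 3000) = 0.01288.
- Two-sided power = Φ((0.05 − 1.96 × 0.01289) / 0.01288) = Φ(1.92) = 97.3%.

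The figure reproduces. It is for a binary outcome; no power or precision is given for mean DOT or a DOT total.

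**2. What can be recovered from the planned output.** Non-receivers score zero, so all per-drug means within a period share one denominator. The mean of a sum is the sum of the means, so the point estimate for any total can be added up from Table 3. The variance cannot:

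Var(Σ dⱼ) = Σ Var(dⱼ) + 2 Σ Cov(dⱼ, dₖ).

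With three targeted drugs and three alternative groups there are 6 variances and 6 × 5 / 2 = 15 covariances. Separate models and separate intervals supply the variances and none of the covariances.

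**3. How much the covariance matters.** The documents give no SD or correlation for DOT, so these are assumptions: n = 3000 per period, patients independent (as in the protocol's own power figure), and equal SD and equal pairwise correlation r for the three targeted drugs. Per-drug half-width h = 1.96 × SD × √(2/3000); half-width for the total = h × √(3 + 6r).

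| SD (days) | per drug | total, r = −0.2 | r = 0 | r = 0.2 | r = 0.5 | three half-widths added |
|---|---|---|---|---|---|---|
| 1.5 | 0.076 | 0.102 | 0.131 | 0.156 | 0.186 | 0.228 |
| 2.5 | 0.127 | 0.170 | 0.219 | 0.259 | 0.310 | 0.380 |
| 3.5 | 0.177 | 0.238 | 0.307 | 0.363 | 0.434 | 0.531 |

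The factor 3 + 6r runs from 0 at r = −0.5 to 9 at r = 1. At SD 2.5 the planned output alone therefore fixes the half-width only to somewhere between 0 and 0.380 day.

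**4. Power, on the same assumptions.** For a true fall of 0.10 day in each targeted drug at SD 2.5, each per-drug comparison has power Φ(0.10 / 0.0645 − 1.96) = 34%. The total has 93%, 77%, 62% and 48% at r = −0.2, 0, 0.2 and 0.5. At SD 1.5 the figures are 73% per drug and 89–100% for the total; at SD 3.5 they are 20% and 27–70%.

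**5. Switching.** Suppose x days per admission move one for one from drug A to drug B. The contrast for A changes by −x and that for B by +x. If both are targeted, total targeted DOT changes by 0. If B is an alternative, total targeted DOT changes by −x, total alternative DOT by +x, and the combined total by 0. Only the combined total is unchanged in both cases, so the three totals are best read together.

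**6. Population.** Take a patient denied a targeted drug who instead receives d days of an alternative. Over all admissions this patient adds 0 to targeted, d to alternative and d to combined DOT. If the tables cover only admissions with a targeted drug, the patient contributes nothing, and the d days that hypothesis 5 concerns are missed.

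**The case against.** The strongest reply is that the SAP is not blind to aggregate use. Protocol 9.4.1.2 lists days of targeted and alternative use, SAP 3.3.2 (objective 5) names integrated measures based on DOT, and SAP 3.3.3 names DOT per patient-days. SAP section 1 says that it covers key analyses and that further reports will follow. This is fair as evidence that totals were not rejected. It does not fill the gap: none of these items has an analysis section in the SAP, and the DOT section cites only objective 2 as its purpose.

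It is also fair that these are secondary analyses in a feasibility study whose primary endpoints are descriptive, and that both documents concede limited ability to show definitive change.

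Three stronger readings are tempting, and the documents do not support them.

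- A reader might infer that hypothesis 4 is untestable too. It speaks of a decrease in targeted antimicrobials and does not mention a total. The planned contrasts of each targeted drug against the historical year address it. A targeted total would summarise it better, since no rule covers mixed per-drug results.
- A reader might count intervals and call the plan a multiplicity hazard. The count depends on whether the anti-MRSA examples are one group or several, the plan is mainly estimation, and multiplicity is a separate question from missing totals.
- A reader might conclude that the shortages bias the per-drug results most. SAP 3.5.2 says that observed differences "may be related to drug availability and not the intervention", but it names no drug, date or hospital. The models adjust for calendar time, and a targeted-only total would also move if patients went to alternatives. Per-drug results remain useful for seeing which drug a shortage affected.

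**Conclusion.** The point holds for hypotheses 5 and 6. As written, SAP section 10 plans no contrast and no confidence interval for the net effect on targeted plus alternative use. The point estimates can be recovered by addition; their uncertainty cannot. That conclusion rests on the text alone. The size of the gap in precision (0.170 to 0.310 day against 0.380 from adding half-widths, at SD 2.5) rests on assumed SDs and correlations and only illustrates why the covariance is needed.

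The population concern is conditional: it applies if included antibiotic means targeted antibiotic. Relative insensitivity to one-for-one switching during shortages is a side benefit of the combined total; the documents do not demonstrate a bias.

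The consequence is moderate. The primary feasibility conclusions are untouched, but a planned report is to focus on DOT, and two of its stated hypotheses would go without an interval.

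**What to change.** In SAP section 10, add three derived outcomes per admission, always reported together:

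1. total targeted DOT, the sum over the three targeted drugs;
2. total alternative DOT, the sum over the listed alternatives;
3. combined DOT, the sum of the two.

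Give each the same three contrasts, 95% intervals and model as the per-drug outcomes. Name them as the main DOT contrasts for hypotheses 5 and 6. For hypothesis 5, read all three for restriction/preauthorization against the historical year; for hypothesis 6, use the combined total for PAR against restriction/preauthorization. Keep the per-drug results as supportive.

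Compute the totals over all admissions, or as DOT per 1,000 patient-days of all admissions from the ADT data. At the least, use all admissions with a targeted or alternative antibiotic. State what included antibiotic means. Close the anti-MRSA list, which is now given as examples, so that the alternative total is defined.

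The cost is small. Protocol 9.4.2 already plans to obtain "start and stop dates for all antibiotics" and admit and discharge dates for all patients, so the work is three derived variables, three more sets of the planned analyses and a few lines of SAP text. I would not add an exclusion of hospital-months in shortage: the documents list no such months, the records would have to be sought, and dropping months could unbalance the crossover.

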### 95% CI for Difference in Proportions (Intervention 1 – Intervention 2)

[figure not shown]

Figure 9-3

[figure not shown]

Site heterogeneity of treatment effects will be explored by modeling outcome as a function of treatment, period, site, and period\*site interaction. Age, sex, and race will also be included to control for confounding by demographic variables. Treatment and period effects will be fixed. Site and period\*site effects will be random.

Exploratory analyses of the overall benefits and risks of the AS interventions will also be conducted using methods that are currently being developed.

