## 3.5 General statistical considerations

- Tables will be presented by Hospital and intervention; each of the 4 sites will be evaluated separately.
  - Stratified pooled analyses may also be conducted
- Dates will not be shown, but converted to days from intervention (intervention) or first hospital contact (feasibility).
- Each Table/Figure/Listing will be annotated with the name and location of the program used to create it, including its location directory.
- All programs that create permanent study-specific derived datasets or that contribute to analyses of the primary or secondary objectives will be validated according to CBAR SOPs
- Categorical variables will be summarized with n and proportion
- Continuous variables will be summarized with mean, sd, median, Q1, Q3, min and max.
- For secondary analyses, there are 3 contrasts of interest
  - PAR vs. historical control
  - Formulary Restriction/Preauthorization (Res/PreA) vs historical control
  - PAR vs Res/PreA
- For each contrast, the difference in outcomes will be estimated using 95% confidence intervals
  - Difference in proportion with 95% CIs for binary outcomes
  - Difference in means with 95% CIs for continuous outcomes

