### 3.5.1 Cluster Randomization and Analysis

This antimicrobial stewardship study was implemented at four hospitals, where each hospital is considered a single cluster. Cluster randomized trials can be analyzed at the cluster level or the patient level. Ideally, analyses are conducted on the cluster level as this is the unit of randomization. However, we will analyze this study using the patient as the unit of analyses as there are only four clusters.

Since randomization occurs at the cluster level but analyses must be conducted at the patient level, the benefits of randomization (i.e., expectation of balance of confounding factors) cannot be assumed. The small sample size of 4 clusters may also negate the benefits of randomization. The crossover nature of the design will help to balance confounding factors as each hospital can serve as its own control. However, as the crossover occurs at the cluster level, and the patients are neither randomized nor crossed-over, it does not have the same advantages as a standard crossover trial and it does not eliminate within-patient variation; the analyses cannot be “paired”.

Since the effect of the intervention is not only a function of the intervention itself but also of the pharmacist, there is potential for considerable site variation in response. Thus each of the four sites will be evaluated separately. Stratified pooled analyses may also be conducted.

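### The SAP's DOT regression lists interactions that this four-hospital crossover cannot separate, and it leaves open the period coding on which the strategy-versus-control contrasts depend

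*Combined protocol and SAP*

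**What the plan says.** SAP section 10 states the aim of the model: "The purpose of the model is to look at the effect of the intervention on DOT for each antibiotic of interest". The listed terms are "Adjusting for hospital, study period, AS strategy, calendar time, demographic variables". The interactions are period by strategy and "hospital \* study period, hospital \* strategy, will be explored". The SAP does not say whether the historical year enters the model, how study period is coded, or which terms are fixed and which random.

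Separately, Table 3 of the same section gives PAR versus history, Res/PreA versus history and PAR versus Res/PreA, by hospital, as simple differences: in proportion treated, and "Difference in Mean DOT with 95% CI".

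Protocol section 9.4.1.3 has its own model: "Site heterogeneity of treatment effects will be explored by modeling outcome as a function of treatment, period, site" and a period-by-site interaction. Treatment and period are fixed there; site and period-by-site are random.

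The design (SAP 3.1 and 3.2) is four hospitals, two in each order of strategies, after a historical year without either strategy at all four.

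**The concern.** A strategy effect can be separated from a period effect only by comparing hospitals that used the strategies in opposite orders. Within one hospital, strategy and period change together. An interaction that lets either effect vary by hospital uses up that comparison. The control condition exists only in the historical year, so control and history may be the same column.

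Where columns are aliased, a printed strategy coefficient reflects whichever constraint was imposed to fit the model. A reader who sees study period in the adjustment list would take it that time had been controlled. Two questions are exposed: whether the strategy effect differs between hospitals, and, under one reading of the SAP, the adjusted comparison of each strategy with the prior year.

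**Working it through.** **The plan's own figure.** No figure is attached to the DOT model. The only design figure is 97% power for 0.50 versus 0.55 with 3000 patients per period (protocol 9.1). It reproduces: 0.05/√((0.25 + 0.2475)/3000) = 3.883, and Φ(3.883 − 1.960) = 0.973. It has no bearing on estimability.

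**Inputs.** Hospitals 1 and 4 used Res/PreA then PAR; hospitals 2 and 3 used PAR then Res/PreA (SAP 3.2). Control occurs only in the historical year (SAP 3.1). A contrast is estimable if adding its vector as a row does not raise the rank of the design matrix. Demographics vary between patients and do not affect these aliases.

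**Periods 1 and 2, by hand.** Let τ be PAR minus Res/PreA and π be Period 2 minus Period 1. The PAR minus Res/PreA difference seen within a hospital has expectation

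- τ + π in hospitals 1 and 4,
- τ − π in hospitals 2 and 3.

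Averaging the two orders gives τ. Now add the interactions.

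- *Hospital by strategy*: τ becomes τ₁ to τ₄. There are four differences and five unknowns. Raising π by δ, lowering τ₁ and τ₄ by δ and raising τ₂ and τ₃ by δ leaves the fit unchanged. No τ for a single hospital is identified; their equally weighted mean is.
- *Hospital by period, fixed*: π becomes π₁ to π₄. Any common τ can be fitted by adjusting these, so τ itself is lost.
- *Period by strategy*: this contrast is the order of strategies, which the hospital terms already contain.

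Rank checks for Periods 1 and 2:

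| Terms | Columns | Rank | PAR vs Res/PreA |
|---|---|---|---|
| hospital, period, strategy | 6 | 6 | estimable |
| + period by strategy | 7 | 6 | only as an average over periods |
| + hospital by strategy | 9 | 8 | only as an average over hospitals; 0 of 4 single hospitals |
| + hospital by period (fixed) | 9 | 8 | not estimable |
| + all three | 13 | 8 | not estimable |

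**With the historical year as a third period level.** The columns satisfy P1 + P2 = PAR + Res/PreA, because every Period 1 or 2 admission falls under a strategy and no historical one does. A constant can move from both strategy effects to both period effects without changing the fit.

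- Hospital, period, strategy: 8 columns, rank 7. PAR versus control and Res/PreA versus control are not estimable; PAR versus Res/PreA is.
- Adding linear calendar time: 9 columns, rank 8, same result. Monthly calendar time does not change it either.
- Adding fixed hospital by period: rank 12, and none of the three contrasts is estimable.

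**Illustration with assumed values, no noise.** Take PAR −0.3 DOT, Res/PreA −0.2, Period 1 shift +0.2, Period 2 shift +0.5. If the Period 1 column is dropped, the PAR coefficient is −0.3 + 0.2 = −0.1. If Period 2 is dropped, it is −0.3 + 0.5 = +0.2. PAR minus Res/PreA is −0.1 both times.

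**Two-level period codings with history kept.** These have 7 columns and rank 7, so all three contrasts are estimable. Pooling history with Period 1 gives −0.3 + 0.2 = −0.1 for PAR versus control in the example. Coding Periods 1 and 2 as −0.5 and +0.5 with history at 0 gives −0.3 + (0.2 + 0.5)/2 = +0.05. Neither returns −0.3, because both assume away the shift from the historical year to the study.

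**Replacement models.** History plus Periods 1 and 2 (4 × 24 = 96 hospital-months), without a period factor: hospital, month of year and three-level strategy have 17 columns and rank 17. Hospital, annual harmonic, linear time and strategy have 9 columns and rank 9. All three contrasts are estimable in both.

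**The case against.** A reader might infer that the plan cannot compare either strategy with control. The documents do not support that. The loss requires historical data in the regression and history as its own period level, and the SAP states neither. SAP sections 5 and 6 use the term study period only for Periods 1 and 2, and section 10 is written to compare the two strategies. On Period 1/2 data the main-effects model is full rank and there is no control contrast in it to lose.

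Nor does it follow that the hypothesis of lower use than in the prior period gets no answer or an arbitrary one. The SAP does not assign the three contrasts to the regression. Table 3 gives a defined number for each hospital and contrast. Those numbers are confounded with time, and the protocol (sections 4 and 9.4.3) and SAP 3.5.2 acknowledge possible temporal bias against history.

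The interactions are to be explored, not fixed parts of the model, so the rank of 8 for all three together describes one possible fit. Losing two of three contrasts belongs to the main-effects model with a three-level period; a fixed hospital-by-period term loses the third as well, and a random one need not.

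It is also tempting to say that the protocol's model has the same defect. It does not: random site and period-by-site effects are close to the structure recommended below. Its problem is narrower, as the verdict states.

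What remains after all this is the aliasing within Periods 1 and 2, which holds however the historical year is coded.

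**Conclusion.** The interactions that SAP section 10 proposes to explore cannot be separated in this design. With study period in the model, none of the four hospital-specific PAR versus Res/PreA effects is estimable, and fixed hospital by period removes the overall effect too. Hospital-specific effects become estimable if study period is replaced by linear calendar time, but only by assuming a common linear trend.

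The result for the control contrasts is conditional. With history as its own period level, both are lost from the main-effects model (8 columns, rank 7), with or without calendar time. Two-level codings restore them by assumption. The acknowledged temporal bias does not tell the reader that a listed period adjustment may be unable to address it.

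The protocol model is said to explore differences in treatment effect between sites, yet its only interaction is random period by site, which cannot be told apart from treatment by site.

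The algebra needs only the allocation in SAP 3.2 and one strategy per hospital per period; the DOT values in the illustration are assumed. The point should be settled before the DOT models are run, but it is not critical: DOT is secondary, the primary analysis is descriptive, and Table 3 stands apart from the regression.

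**What to change.** Reword SAP section 10 as follows.

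1. *PAR versus Res/PreA*: Period 1 and 2 data only; hospital, period, strategy and demographics; hospital by period only as a random or error term. Delete the three exploratory fixed interactions.
2. *Each strategy versus control*: historical plus Period 1 and 2 data; hospital, calendar month, three-level strategy and demographics; no study-period factor. Add a sensitivity analysis with an annual harmonic and linear time. State the secular-trend assumption behind each.
3. State, in the SAP and for the model in protocol 9.4.1.3, that hospital-specific strategy effects cannot be separated from hospital-specific period effects.

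No new data are needed. Two costs should be stated. The control estimates then rest openly on a trend assumption. In the first model, 8 hospital-period cells less rank 6 leave 2 degrees of freedom for the hospital-by-period term, so that variation will be poorly estimated.
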